### Coenrolment

As the HeadPoST trial is a cluster randomised controlled trial of an organizational change, there are no methodological contraindications to coenrolment of patients into individual patient randomised controlled trials. Although the aim is to recruit all consecutive stroke patients, allowance is made for coenrolment of patients into individual patients’ randomised pharmaceutical investigational or rehabilitation trials, or into observational registry studies, provided that this is acceptable to participants (who will likely have to complete additional follow-up requirements), the local REC, cluster guardians and competing trial sponsors/chief investigators. As most conventional individual patient randomised clinical trials recruit only a minority (e.g., 2-10 %) of all patients, it is anticipated that only a few patients could be enrolled in multiple research studies or clinical trials. If coenrolment is unacceptable and patients are included in another trial, then an explanation is to be given in the screening log regarding why selected patients were excluded from HeadPoST.

### Statistical considerations

#### Sample size

In patients with AIS, lowering the head from 30° to 15° or 0° has been associated with up to 12 cm/s increases in mean CBF in the middle cerebral artery on TCD [12, 36–38]. Other studies have shown that a 1 cm/s increase in CBF is associated with a 0.7-point reduction in NIHSS score [9] and a 16 % reduction in death or dependency based on the mRS [39], whereas the score distributionin the sitting-up head position has been reported to be 0 (18 %), 1 (18 %), 2 (16 %), 3 (15 %), 4 (12 %), 5 (12 %) and 6 (death, 9 %) [40]. For a cluster size of 60 patients with AIS for each intervention (i.e., lying-flat or sitting-up), and assuming 5 % crossover and 10 % dropout rates in each hospital, recruitment failure in 10-15 % of hospitals, and an intracluster correlation coefficient of 0.03 (conservatively estimated from an intracluster correlation coefficient of 0.018 in another cluster controlled trial [41] undertaken across 19 ASUs in New South Wales, Australia), a sample size of 16,800 patients with AIS at 140 sites will provide 90 % power (α 0.05) to detect at least 16 % improvement (shift) in death and disability on the mRS at day 90 in the ordinal logistic regression analysis [42, 43]. There will also be 90 % power to detect at least 16 % improvement (shift) in neurological function on the NIHSS at day 7, at least 30 % reduction in death and at least a 2-day reduction in length of stay for such patients.

For patients with acute ICH, the cluster size will be smaller and may vary across sites (10-30 %), particularly between China and elsewhere [1, 44], depending on the frequency of ICH. Assuming a recruitment of 10 ICH patients on average per site for each intervention period, a sample size of 2,800 patients with ICH at 140 sites will provide 90 % power (α 0.05) to detect at least 25 % improvement (shift) in death or disability associated with the sitting-up head position. Moreover, there will be 90 % power to detect at least 25 % improvement in NIHSS at day 7, at least 33 % decrease in death and at least a 2-day reduction in length of stay for these patients.

The power of the trial is derived from having a very large number of clusters, which we consider achievable because the workload at each site will be kept low and for a short period of time. The inflation of the cluster size and the number of clusters are being done to take account of stroke mimics, poor recruitment and quality issues. An overall target of 70 patients in each intervention group is derived from the requirement of 60 and 10 with AIS and ICH, respectively. For the smaller ASUs with fewer than 200 people admitted with stroke per annum, the sample size will likely be achieved over 4 to 5 months, so, taking account of the crossover and 90-day follow-up, the total duration of the study is approximately 12 months. For large ASUs, and especially for the hospitals in China with over 1,200 stroke admissions per annum, the required total number of 140 (2×70) patients to be recruited is likely achieved just over several weeks, for a study duration of 4 to 5 months.

#### Data analysis

We will analyse patients in the treatment group to which they are allocated according to the intention-to-treat principle. We will compare patients allocated to lying-flat with those allocated to sitting-up. The primary analysis will be unadjusted, but adjusted analyses can also be carried out on the primary and secondary outcomes if required. All analyses will be adjusted for clustering within sites. No adjustment for multiplicity is planned, as there are only a small number of prespecified efficacy outcomes being investigated. All analyses will be undertaken at the patient level on an intention-to-treat basis, as defined by allocated head position at each hospital, using generalised estimating equations (GEE) or random-effects regression to account for clustering.

The primary outcome of death or disability according to the mRS [26] score at 90 days will be analysed by means of GEE for ordinal data (i.e., the natural extension of ordinal logistic regression [‘shift’] analysis for clustered data), in which mRS as a dependent variable with seven levels (ranging from 0 [no residual symptoms] to 6 [death]). The secondary outcome of the NIHSS [27] score at 7 days will also be analysed similarly, as the NIHSS [27] is considered as an ordinal endpoint with seven levels [45]. Binary secondary outcomes will be analysed by means of standard GEEs with a logistic link and/or time-to-event type endpoints using the Cox model with a sandwich formula [46]. For continuous outcomes, a random intercept linear regression model will be used. Descriptive statistics will be provided for safety data. The number of patients reporting any SAEs and the occurrence of specific SAEs will be tabulated. Tests of a treatment effect on specific SAEs may be attempted by means of a χ^2^ test adjusted for clustering. Subgroup analyses will also be conducted to investigate the effects of the interventions in different pathological subtypes of AIS, defined as small vessel ‘lacunar’, large vessel, cardioembolic and other.

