**Methods/Design:**

We plan to conduct an international, cluster randomised, crossover, open, blinded outcome-assessed clinical trial involving 140 study hospitals (clusters) with established acute stroke care programs. Each hospital will be randomly assigned to sequential policies of lying-flat (0°) or sitting-up (≥30°) head position as a ‘business as usual’ stroke care policy during the first 24 hours of admittance. Each hospital is required to recruit 60 consecutive patients with acute ischaemic stroke (AIS), and all patients with acute intracerebral haemorrhage (ICH) (an estimated average of 10), in the first randomised head position policy before crossing over to the second head position policy with a similar recruitment target. After collection of in-hospital clinical and management data and 7-day outcomes, central trained blinded assessors will conduct a telephone disability assessment with the modified Rankin Scale at 90 days. The primary outcome for analysis is a shift (defined as improvement) in death or disability on this scale. For a cluster size of 60 patients with AIS per intervention and with various assumptions including an intracluster correlation coefficient of 0.03, a sample size of 16,800 patients at 140 centres will provide 90 % power (α 0.05) to detect at least a 16 % relative improvement (shift) in an ordinal logistic regression analysis of the primary outcome. The treatment effect will also be assessed in all patients with ICH who are recruited during each treatment study period.

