## Methods/Design

### Trial design

HeadPoST is an international, multicentre, prospective, cluster randomised, crossover, blinded outcome-assessed trial to be conducted through a global network of investigators, with hospitals as the unit of randomisation (clusters). All hospitals will participate in both the lying-flat (0°) and the sitting-up (≥30°) head position treatment phases. They will enrol and implement the intervention until the target number of patients is reached before crossing over to the opposite intervention. The study scheme outlines the flow and crossover of interventions (Fig. 1).

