### Consent process and participant inclusion and exclusion criteria

Each participating site must obtain written approval from its research ethics committee (REC) (e.g., institutional review board [IRB]), as well as from any other relevant regional or national bodies, before patient recruitment can commence. A list of all ethical bodies that have approved the study is provided in Additional file 1. A mixed consent process is proposed, according to local and/or national rules and regulations, as outlined in Table 1. Consent under the cluster guardian format or appropriate approval is necessary to prevent contamination of the intervention across patients nursed in closed proximity and by busy clinicians caring for multiple patients [28]. It is also likely to avoid responder bias in patients (or their surrogates) as a result of potentially thinking that they have received nonstandard care [29]. Under the guardian consent process, all eligible patients will receive the intervention as standard of care and will be provided with an approved Patient Information Sheet (PIS) and Consent Form as soon as practical after admission. According to the local REC-approved consent process, patients’ written consent to be either included or excluded—opt-in or opt-out patient consent, respectively—will be obtained before enrolment to collect their medical and personal information and to contact them again for follow-up at 90 days. These patients will also be able to formally opt out at any stage of the study.

**Table 1 Tab1:** Consent options for the HeadPoST trial

*Hierarchy of consent options proposed in this study*	
1.	Cluster guardian consent or appropriate approval (e.g., signed by general manager or chief executive of hospital or by head of neurology/stroke department) for the randomised head position to be the usual nursing care for patients with acute stroke, obtained before commencement of the study
With any of the following:	
2.	*a. Recommended*: Opt-out consent obtained from patients for the collection of data through in-person assessment and extraction of information from medical records during the hospital stay and follow-up, and release of personal information to allow centralised follow-up at 90 days after initial admission to the hospital for research purposes

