### Randomisation

The unit of randomisation is the hospital. A statistician not otherwise involved in the trial will generate the randomised allocation sequence and treatment group assignment of either lying-flat (0°) or sitting-up (≥30°) as the first intervention before crossover to the other intervention. Participating sites will be stratified according to country, and the allocation sequence will be concealed until the interventions are assigned.

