### Data collection and follow-up

Sites should record details of all patients admitted with acute stroke, and all patients should be placed in the randomised head position unless there is a clear contraindication (e.g., cardiac or respiratory failure). All patients will be approached for enrolment for data collection within the trial by site study coordinators and investigators. Brief demographic details of all stroke patients who are approached but who are not enrolled, and the reason for nonenrolment, will be recorded on a screening and enrolment log to determine selection bias. For safety analysis, sites are requested to provide information on any death known among registered nonenrolled patients during follow-up. To assist the implementation of the intervention at each site, information will be gathered on the organisational structure of the site and the various clinical wards that will be involved in the intervention. Each site’s lead investigator is required to complete a hospital organisation questionnaire, developed based upon previous surveys in this field [32–34], to assist the regional coordinating centre (RCC) in preparing the training and site initiation visit (see Additional file 2).

The goal of the main assessments of participants in the first 24 hours will be to promote adherence to the allocated head position. A monitoring chart will be maintained by clinical staff to record the duration in the allocated head position, but importantly also the time spent out of position with a description of the reason. Basic physiological parameters will also be recorded. Sites are also required to collect a limited amount of data on patients at the time of admission (day 1) and separation (day 7 or at discharge, transfer or death, if earlier), as well as all SAEs, including death, until 90 days.

Appropriately trained outcome assessors, who are kept blind to the management of patients, will use a script to conduct a telephone assessment of health and functioning at 90 days.

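### The primary mRS analysis is fixed as unadjusted, with adjustment left to an undefined condition, in an open trial that enrols patients while the hospital's policy is known

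*Protocol article*

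**What the plan says.** Protocol article, Data analysis: "The primary analysis will be unadjusted, but adjusted analyses can also be carried out on the primary and secondary outcomes if required". Nothing says what would require an adjusted analysis, when that would be decided, or which covariates would enter. The same section says "All analyses will be adjusted for clustering within sites" and names a GEE for ordinal data with seven mRS levels as the primary model.

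Trial design: "All hospitals will participate in both the lying-flat (0°) and the sitting-up (≥30°) head position treatment phases". The abstract describes the trial as open, with blinding of outcome assessment only. Randomisation: "Participating sites will be stratified according to country"; what is randomised is the order of the two policies.

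Under Consent process and participant inclusion and exclusion criteria, patients receive the position as standard care, and their written opt-in or opt-out "will be obtained before enrolment to collect their medical and personal information and to contact them again for follow-up at 90 days". The exclusion criteria include a clinical judgement that one of the positions is indicated or contraindicated. Under Data collection and follow-up, sites must "collect a limited amount of data on patients at the time of admission (day 1"), and non-enrolled patients are logged so that selection bias can be assessed.

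**The concern.** In a cluster crossover trial each hospital serves as its own control, so stable differences between hospitals cancel. The mix of patients within a hospital need not cancel. Here staff know the current policy when they judge contraindications and approach patients. Patients decide about data collection once the policy is in force. The Background reports clinicians' concern about aspiration pneumonia when patients lie flat, and Data collection and follow-up gives cardiac or respiratory failure as an example of a contraindication. It is plausible, though not shown, that exclusions or refusals could fall unevenly between the two policies and involve sicker patients.

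An unadjusted primary model carries any such imbalance into the odds ratio, and a larger sample does not remove it. The screening log may reveal the problem but does not correct the primary result. Because the condition on adjustment is undefined, whether an adjusted analysis is done, and with which covariates, could be settled after the baseline tables or results have been seen.

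**Working it through.** **Inputs from the protocol article (Sample size).** Control mRS distribution 18/18/16/15/12/12/9%; 16% shift; 90% power; α 0.05; 60 AIS patients per hospital per policy; ICC 0.03; 5% crossover; 10% dropout; recruitment failure in 10-15% of hospitals; 140 hospitals; 16,800 patients. Assumed: the shift means OR 0.84 and the test is two-sided.

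**1. Reproduce the plan's own figure, without covariates.** Whitehead's formula is N = 12(z₀.₉₇₅ + z₀.₉₀)² / [(log OR)²(1 − Σp̄³)]. Here (1.960 + 1.282)² = 10.51, log(1/0.84) = 0.174 and 1 − Σp̄³ = 0.975, so N ≈ 4,253.
- With m = 54 (60 less 10% dropout), the design effect is 1 + 53 × 0.03 = 2.59. Take log OR × 0.90 for crossover in both directions, dropout 0.9 and hospital failure 10%: 4,253 × 2.59 / 0.90² / 0.9 / 0.9 ≈ 16,790.
- With m = 60, the design effect is 2.77. With log OR × 0.95 and hospital failure 12.5%: 4,253 × 2.77 / 0.95² / 0.9 / 0.875 ≈ 16,575.

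Both are close to 16,800, so 90% power is met by the unadjusted test. This design effect is that of a parallel cluster trial and takes no credit for the within-hospital crossover. With an assumed correlation between a hospital's two period effects of 0.5-0.8, the first setting gives unadjusted power of about 97-99.6%.

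**2. Standard error of the primary estimate.** Patients analysed: 140 × 0.9 × 2 × 54 = 13,608. With 1 − Σp³ = 0.977 for the control distribution, SE = √[12 × 2.59 / (13,608 × 0.977)] ≈ 0.048, against a target log OR of 0.174.

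**3. Effect of a systematic case-mix imbalance (assumed range).** Let s be the covariate's log OR per SD and d the between-policy imbalance in SD. The bias is b ≈ s × d × a, where a is the attenuation from omitting the covariate (simulated: 0.886, 0.795 and 0.69 at s = 0.8, 1.2 and 1.6). Type I error = Φ(b/SE − 1.96) + Φ(−b/SE − 1.96).

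| s | d = 0.02: bias, type I | d = 0.05: bias, type I |
|---|---|---|
| 0.8 | 0.014, 6.0% | 0.035, 11.3% |
| 1.2 | 0.019, 6.8% | 0.048, 16.7% |
| 1.6 | 0.022, 7.4% | 0.055, 20.7% |

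The bias is 8-13% of the target log OR at d = 0.02 and 20-32% at d = 0.05. At d = 0.10, type I error would be 31-63%. If the crossover makes the SE smaller than planned, the same bias produces more false positives. For scale, chance alone gives an imbalance with SD of about √(2/6,804) = 0.017 in a covariate that varies independently between patients. Chance imbalance is already covered by the SE; the table concerns a systematic shift of that order or larger.

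**4. Efficiency gain under the plan's clustering (linear approximation, total variance 1).** The variance of a hospital-period mean is 0.03 + 0.97/60 = 0.0462, of which 0.03/0.0462 = 65% is at cluster level. If covariates explain a share R² of the within-cluster part only, the gain is 0.0462 / [0.03 + 0.97(1 − R²)/60]. That is 1.04, 1.08 and 1.12 at R² = 0.1, 0.2 and 0.3. Power = Φ(3.24√gain − 1.96), or about 91%, 92% and 93%. If covariates also explained hospital-period variance, so that the gain were 1.25-1.5, power would be about 95-98%.

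**5. Country.** In a simulated crossover with 126 hospitals in eight countries and equal-sized periods, the estimates with and without country agreed to 1e-14, and the empirical SD was 0.0338 either way.

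**The case against.** The strongest reply is that an unadjusted primary analysis is a recognised choice, is stated without ambiguity, and reaches its planned power. Only supportive analyses are optional, and their covariate lists normally sit in a statistical analysis plan, which is not shown. The protocol also has safeguards: consecutive recruitment, one exclusion criterion worded for both positions, guardian consent with opt-out recommended, and a log of non-enrolled patients that includes their known deaths.

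Much of this stands. The absence of a covariate list is no finding, the safeguards reduce the risk of selection, and the primary result itself is not open to choice. What remains is that the protocol fixes the unadjusted model as primary and makes any adjusted one conditional on an undefined need. A later plan could not make the adjusted model primary without departing from this text.

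Three stronger readings are tempting, and the documents do not support them.
- *The trial wastes power.* The stated 90% is reached without covariates. The larger gains seen when patients are treated as independent do not carry over to a design effect of 2.6 to 2.8.
- *Ignoring the stratification factor damages the analysis.* Country stratifies only the order of policies, every hospital is to deliver both, and clustering by site is modelled. Exact equality needs equal-sized periods, so a hospital that stops after one period would disturb it. That does not make country a material omission.
- *The unadjusted odds ratio is biased towards the null.* Marginal and conditional odds ratios differ because the odds ratio is non-collapsible. The marginal one is not biased for its own target, and it is a legitimate target for a hospital-wide policy.

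**Conclusion.** The point holds as a protection against measured case-mix imbalance in an open trial, and it should be acted on. Its size rests on assumptions, because the documents give neither the prognostic strength of the admission variables nor any expected imbalance. Within the assumed range of 0.02-0.05 SD and log OR 0.8-1.6 per SD, type I error is about 6% to 21%; at the low end the effect is slight. Nothing in the documents shows that selective enrolment will occur. The efficiency gain is a modest and uncertain bonus, about 91-93% power against 90%, or more if the covariates explain hospital-period variance. A reader should not infer that the trial is underpowered or that leaving out country harms it. Nor should a reader infer that adjustment would remove selection bias altogether, because it reaches only what was measured.

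**What to change.** Before unblinding, make the primary analysis the ordinal GEE with terms for policy, period, age and whatever baseline severity measure is recorded at admission. The article mentions only a limited set of day-1 data and names no severity scale, so the covariate must be taken from what sites actually record. Keep the unadjusted model as a prespecified sensitivity analysis and delete the words *if required*. Country may be added but is not needed.

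The cost is analysis wording and no new data. The odds ratio becomes conditional on the covariates and, if there is an effect, is expected to lie further from 1 than the unadjusted one, so the estimand must be stated. A simple rule for missing covariate values must be written down. The report should say that unmeasured differences between the policy periods remain uncorrected.

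### The site-only random-intercept model named for continuous secondary outcomes understates the standard error if patients in the same hospital-period are more alike than patients in different periods of that hospital

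*Protocol article*

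**What the plan says.** Trial design sets a two-period cluster crossover: "All hospitals will participate in both the lying-flat (0°) and the sitting-up (≥30°) head position treatment phases". The order of the two policies is what is randomised (Randomisation).

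Data analysis makes three statements that bear on the standard errors:

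- For every analysis: "All analyses will be adjusted for clustering within sites".
- On the permitted methods: "using generalised estimating equations (GEE) or random-effects regression to account for clustering".
- For continuous outcomes: "For continuous outcomes, a random intercept linear regression model will be used".

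The same section assigns the 90-day mRS and the 7-day NIHSS to ordinal GEE, binary outcomes to logistic GEE, and time-to-event outcomes to a Cox model with a sandwich variance. Site is the only level of clustering named; no period or hospital-by-period term appears.

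Sample size gives one correlation, "an intracluster correlation coefficient of 0.03 (conservatively estimated from an intracluster correlation coefficient of 0.018 in another cluster controlled trial", for the AIS calculation on the mRS. It gives no separate correlation between patients treated in different periods of the same hospital. Length of stay is a secondary outcome (Trial outcomes) with its own 90% power claim for a two-day reduction (Sample size). No multiplicity adjustment is planned.

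**The concern.** In this design the treatment effect is estimated from the difference between a hospital's two periods. Stable differences between hospitals cancel. Variation that belongs to one hospital in one period, such as season, staffing or case mix, does not cancel and adds directly to the error of the contrast.

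A model whose only random effect is a hospital intercept has no place for that second component. It assumes that two patients in the same period are no more alike than two patients in different periods. When that is false, its model-based standard error is too small however many hospitals take part.

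At stake are the confidence intervals and p-values for length of stay, for EQ-5D if it is treated as continuous, and for any other outcome for which random-effects regression is used instead of GEE.

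**Working it through.** **Inputs from the article.** 140 sites, 60 AIS patients per site per policy, an average of 10 ICH patients per site per policy, ICC 0.03 (source value 0.018), 5% crossover, 10% dropout, and recruitment failure in 10-15% of hospitals (all Sample size).

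**Assumptions.** The between-period correlation η is not given, so the ratio η/ρ is varied from 1 to 0, where ρ is the within-period ICC. The ICC of 0.03 belongs to the mRS calculation; its use for length of stay or EQ-5D is illustrative. The random intercept is read as a hospital intercept with model-based standard errors.

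**1. The plan's own sample size.** Take a common odds ratio of 0.84, two-sided α 0.05, 90% power and the stated mRS distribution. The Whitehead formula gives N = 12 × 10.507 / (0.0304 × 0.9753) ≈ 4,253.

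- Design effect: 1 + 59 × 0.03 = 2.77, so 4,253 × 2.77 ≈ 11,780.
- Crossover and dropout: 11,780 / (0.95² × 0.90) ≈ 14,503.
- Site failure of 10, 12.5 and 15%: 16,115, 16,575 and 17,063.

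The stated 16,800 lies in this range. A design effect of 2.77 is what a cluster crossover has when η = 0, so the target takes no credit for between-period correlation.

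**2. True and reported variance.** With m patients per hospital-period and total variance 1, the variance of the treatment contrast is proportional to

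T = 1 + (m − 1)ρ − mη.

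The hospital-intercept model reports a variance proportional to its pooled within-hospital residual, approximately

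M = (1 − ρ) + m(ρ − η)/(2m − 1).

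Type I error at nominal 5% is 2[1 − Φ(1.96/√(T/M))].

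Worked case, m = 60, ρ = 0.03, η = 0.015: T = 1 + 1.77 − 0.90 = 1.87; M = 0.97 + 60 × 0.015/119 = 0.978; T/M = 1.91; the true standard error is √1.91 = 1.38 times the reported one; type I error is 15.7%.

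| η/ρ | η | T (m = 60) | True SE / reported SE | Type I error, m = 60 | Type I error, m = 10 |
|---|---|---|---|---|---|
| 1 | 0.030 | 0.97 | 1.00 | 5.0% | 5.0% |
| 0.9 | 0.027 | 1.15 | 1.09 | 7.2% | 5.3% |
| 0.8 | 0.024 | 1.33 | 1.17 | 9.4% | 5.7% |
| 0.5 | 0.015 | 1.87 | 1.38 | 15.7% | 6.7% |
| 0 | 0 | 2.77 | 1.68 | 24.3% | 8.4% |

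The simpler approximation M = 1 − η gives 15.5% and 23.9% in the last two rows for m = 60. With the source ICC of 0.018 and m = 60, ratios of 0.8, 0.5 and 0 give 7.6%, 11.5% and 17.4%.

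**3. Simulation of the linear model** (140 hospitals, 60 per period, ICC 0.03, 20,000 runs). At ratios 1, 0.9, 0.8, 0.5 and 0 the hospital-intercept test rejected in 5.2, 7.1, 9.4, 15.6 and 24.4% of runs. A sandwich variance grouped by hospital rejected in 5.2-5.5% throughout.

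**4. Simulation of the ordinal route** (proportional-odds fit with independence working correlation and hospital-level sandwich, standing in for the ordinal GEE; 2,000 runs, Monte Carlo error about 0.5 points). Type I error was 6.0, 6.1 and 4.9% at ratios 1, 0.8 and 0.5. With an unmodelled period effect (log odds ratio 0.2) at ratio 0.5 it fell to 2.9% with equal sizes and 3.5% with unequal sizes and 120 sites.

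**The case against.** **A reader might infer that the whole analysis, including the primary test, is anti-conservative.** The article does not support that. It assigns the mRS, NIHSS and binary outcomes to GEE and time-to-event outcomes to Cox with a sandwich. With about 140 hospitals, a robust variance grouped by hospital covers correlation both within and between periods. One reservation stands: the sandwich is named only for Cox, so robust standard errors for the GEEs are inferred from usual practice.

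**A reader might infer that omitting a period term inflates type I error.** It does not. The order of policies is randomised, and in the simulations with a sandwich variance an ignored period effect made the test conservative. The omission costs precision, not validity.

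**A reader might infer that the sample size contradicts the analysis model.** The 2.77 belongs to the mRS, which goes to GEE; the random intercept belongs to continuous outcomes. Taking no credit for between-period correlation is cautious planning, not a contradiction.

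**The inflation is conditional and its size is borrowed.** This stands. It vanishes if the two correlations are equal, and the 24% figure requires no correlation at all between a hospital's two periods. The Background justifies the crossover by differences between hospitals in organisation and background care, which argues for a positive η. Large hospitals are expected to finish in several weeks, leaving little time for drift. Against that, smaller units are expected to need 4 to 5 months to reach their target, so their two policies may fall in different seasons.

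**The general sentence on methods may not offer a free choice.** The following paragraph matches methods to outcome types, so the random-effects option may refer only to continuous outcomes. That is a fair reading; the point then covers those alone.

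**This may be detail for the statistical analysis plan.** The level of the intercept, the variance estimator and a period term could be set there. Silence on them would be no finding. But the article does name a model for continuous outcomes, and site is the only clustering level it gives. As worded, that model omits the component of variance that matters in this design.

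**Conclusion.** The point holds for continuous secondary outcomes, and for any analysis in which random-effects regression with a site intercept replaces GEE. Standard errors there are too small whenever correlation is higher within a hospital-period than across periods. For the illustrative AIS case the standard error would need multiplying by about 1.17 at a correlation ratio of 0.8 and 1.38 at 0.5. In ICH, with about 10 patients per period, the effect is small.

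This rests on reading the model as a hospital-only intercept with model-based standard errors, and on an ICC that the article does not state for these outcomes. The true size for length of stay and EQ-5D is therefore unknown. No inflation is shown for the primary outcome. Severity is moderate: a secondary-outcome model to correct before analysis, not a threat to the trial's main conclusion.

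**What to change.** - Replace the random-intercept linear model with a linear mixed model that has a fixed period effect and random effects for hospital and for hospital-by-period. Alternatively, keep the simpler model and use robust standard errors clustered on hospital.
- Apply the same rule wherever random-effects regression is used instead of GEE.
- State that GEE and Cox inference uses the sandwich variance grouped by hospital, with both periods in one group.
- State whether EQ-5D is analysed as continuous, so that it is clear which rule applies.

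This changes analysis wording only; recruitment, data collection and sample size are untouched. The cost is somewhat wider intervals for the affected secondary outcomes when hospital-by-period variation is present.
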